
### Additional variables

Descriptive variables and possible confounders and modifiers for exploratory analyses will be collected. Descriptive variables will include: education, living status, history of smoking, use of ambulatory devices, use of municipal help, history of falls during the last year, Nutritional Risk Screening (NRS) [88–90], the New Mobility Score (NMS) (recall of mobility 2 weeks before admission and on the day of admission) [91, 92] and the Cumulated Ambulation Score (CAS) [93]. Possible confounders and modifiers will be assessed: gender; age; cognition by the Short Orientation-Memory-Concentration test (OMC) [94], the Mini Mental State Examination (MMSE) [95], the Trail Making Test (Trails) [96, 97], the Digit Symbol Substitution Test (DSST) [98], and the Hopkins Verbal Learning Test – Revised (HVL-R) [99, 100]; depression by the Geriatric Depression Scale (GDS) [101]; health status by the EuroQol instrument (EQ-5D) [102]; nutritional state by the Mini Nutritional Assessment (MNA) [103]; self-reported physical activity by a four-level questionnaire [104, 105]; pain before and after training by the Verbal Ranking Scale (VRS) [106, 107]; medications, history of training before admission, and history of training in the municipality after discharge. Moreover, baseline level of DEMMI and 24-h mobility using assessments from the first week after discharge will be treated as possible confounders and modifiers. Based on the cognitive assessments, patients will be categorized as having mild cognitive impairment (MCI) or not, and those with MCI will be further sub-categorized as amnestic-MCI, non-amnestic MCI or multiple-MCI [108]. These categories will be used in the analyses.

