### Outcome measures

Outcomes measures will be assessed on admission (baseline), shortly after discharge, approximately 4 weeks after discharge (primary end point) and 6 months after discharge. All outcomes to be assessed are presented in Table 2.

**Table 2 Tab2:** Variables to be assessed

Variable	Baseline	Discharge	4 weeks	6 months
Primary outcome				
de Morton Mobility Index (DEMMI)	+	+	+	+
Secondary outcomes				
24-h mobility (*activ*Pal3™ monitors; 1-week assessments)	+	+	+	+
Isometric knee extension strength	+	+	+	+
30-sec sit-to-stand test	+	+	+	+
Habitual gait speed (HGS)	+	+	+	+
Hand-grip strength (HG)	+	+	+	+
Activities of Daily Living (Barthel Index 20)	+	+	+	+
Descriptive variables				
Age	+			
Gender	+			
Weight	+	+	+	+
Educational level	+			
Living status	+	+	+	+
History of smoking	+			
Use of ambulatory devices	+	+	+	+
Use of municipal help	+	+	+	+
History of falls during the last year	+	+	+	+
Falls Efficacy Scale	+	+	+	+
Nutritional Risk Screening (NRS)	+	+	+	+
New Mobility Score (NMS)	+	+	+	+
Cumulated Ambulation Score (CAS)	+	+	+	+
Days per week spent outdoors	+	+	+	+
Hospitalization within last 4 weeks			+	
Hospitalization within last 6 months	+			+
Possible confounders and modifiers				
Age	+			
Gender	+			
Cognition				
Short Orientation-Memory-Concentration test (OMC)	+			
Mini Mental State Examination (MMSE)		+	+	+
Trail Making Test (Trails)		+	+	+
Digit Symbol Substitution Test (DSST)		+	+	+
Hopkins Verbal Learning Test (HVLT)		+	+	+
Geriatric Depression Scale (GDS)		+	+	+
Health status (EQ-5D)	+	+	+	+
Self-rated health (EQ-5D)	+	+	+	+
Mini Nutritional Assessment (MNA)	+	+	+	+
Self-reported physical activity	+	+	+	+
Verbal Ranking Scale (VRS)	+	+	+	+
Medications	+	+	+	+
History of training before hospitalization	+			
History of training in the municipality after discharge		+	+	+

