### Data collection

The primary investigator and a team of three assistant investigators will perform all baseline and follow-up assessments. All four investigators are trained physiotherapists with 1 to 15 years of experience.

The admission assessments will be performed on the acute medical admissions ward or on an internal medicine ward at Copenhagen University Hospital, Hvidovre, Denmark, within the first 48 h after admission. All follow-up assessments will be performed in the patient’s own home, and the same investigator will assess the same patient at all assessments whenever logistically possible, to promote patient retention.

During each training session the supervising physiotherapist will complete an exercise diary consisting of information about the level of exercise attained according to the progression models, the extra load added (kg), and the number of sets and repetitions performed at each level. Self-reported pain will be registered immediately before and after each training session by the use of the VRS. Moreover, the physiotherapist will register reasons for non-participation as well as the amount of protein consumed after each training session. The patient time line including data collection is presented in Table 3.

**Table 3 Tab3:** Patient timeline

	Study period						
Time point	Admission	Baseline	Hospital intervention	Discharge assessment	Home intervention	4-week assessment	6-month assessment
		≤48 h after admission	Daily during hospitalization	In patient’s home	3 times per week for 4 weeks in patient’s home	In patient’s home	In patient’s home
Enrollment							
Eligibility screen	X						
Informed consent	X						
Study groups							
Strength training		X	X	X	X	X	X
Control		X		X		X	X
Assessments							
Baseline assessment^a^		X					
Primary outcomes		X		X		X	X
Secondary outcomes		X		X		X	X
Descriptive variables and possible confounders and modifiers		X		X		X	X

^a^See Table 2 for a detailed description of assessed variables

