### Secondary and supplementary analyses

From the primary analysis model, the effect during hospitalization and the post-intervention effect (change from 4 weeks to 6 months post discharge) will be estimated. For the secondary outcomes, similar analyses will be performed. Moreover, all analyses will be using adjustments for baseline DEMMI. To account for imbalances in in-hospital time, a sub-analysis will be performed for the effect during hospitalization and the effect from baseline to end of intervention adjusted for length of stay. Additionally, the unadjusted repeated model will be carried out following the per protocol principle, comparing patients who have fulfilled the compliance criteria with the control group. All between-group differences will be expressed as the average difference in change from baseline. The analyses outlined above will all be reported in the main trial manuscript regarding effect of the strength training program.

If additional funding is obtained, more patients will be included to increase the sample size to obtain sufficient power to model statistical interactions and perform secondary analyses (described below), which will be published subsequently. To investigate the possible influence of confounders and modifiers on the effect of the intervention on DEMMI, an unadjusted analysis of variance of the between-group change from baseline to 4 weeks post discharge in the DEMMI score will be performed. In addition, this model will be extended by adjusting for all and each of the potential confounders and modifiers one by one. Confounding effects will be evaluated by comparing the unadjusted effect of group with the adjusted effects. Moreover, to investigate whether or not the effect of the intervention is modified by the potential confounders and modifiers the adjusted models will be extended with an interaction term between group and the potential confounders and modifiers. Similar analysis will be performed with 24-h mobility (average time spent standing or walking per 24 h) and with those of the secondary outcomes that showed a significant between-group difference in the primary analysis. Also, a logistic regression with compliance as the outcome and each of the potential confounders and modifiers as covariates will be performed. All analyses will follow both the intention-to-treat and the per protocol principle.

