To investigate the effect of the intervention on cognition (MCI status, MMSE, OMC, HVLT, DSST, Trails A and B) at 4 weeks, the following analyses will be performed. A generalized logistic regression for MCI status and an analysis of variance for MMSE, OMC, HVLT, DSST, and Trails A and B will be used with group as the independent variable. The analyses will follow the intention-to-treat principle with multiple imputation for missing values. Moreover, these analyses will also be performed adjusting for baseline OMC, baseline DEMMI, gender and age, depression, health status, nutritional state, self-reported physical activity, pain, medications, length of stay and 24-h mobility using assessments from the first week after discharge, and possible interactions with group will be analyzed. Additionally, the models will be repeated following the per protocol principle comparing patients. All results will be expressed as estimated means’ differences between the intervention and control group with the corresponding 95 % confidence intervals.

All models will be investigated for goodness-of-fit (linearity, variance homogeneity and normal distribution of residuals) by visual inspection of plots and remodeling will be performed accordingly. All statistical tests will be performed using SAS (SAS Institute Inc., Cary, NC, USA) and *p* values ≤0.05 will be considered statistically significant. However, for all analyses evaluating potential modifiers and confounders of the intervention *p* values ≤0.01 will be used to account for multiple testing. No interim analysis will be made.

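### Pain recorded after randomization is classed as a possible confounder or modifier, and the session measure does not exist for controls; only baseline pain suits the between-group models, and pain needs a descriptive tolerability report

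*Protocol article*

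**What the plan says.** Pain on the Verbal Ranking Scale (VRS) appears in four places in the protocol article.

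- **Data collection:** "Self-reported pain will be registered immediately before and after each training session by the use of the VRS". The supervising physiotherapist also completes a diary at each session.
- **Outcome measures, Table 2:** the row "Verbal Ranking Scale (VRS)" stands under possible confounders and modifiers. It is marked at all four assessments and not restricted to one arm.
- **Additional variables:** the section opens with "Descriptive variables and possible confounders and modifiers for exploratory analyses will be collected". It then gives the pain item as "pain before and after training by the Verbal Ranking Scale (VRS)", again as a possible confounder or modifier.
- **Secondary and supplementary analyses:** the first paragraph ends with "The analyses outlined above will all be reported in the main trial manuscript regarding effect of the strength training program", and none of the analyses above that sentence uses pain. The next paragraph begins "If additional funding is obtained, more patients will be included to increase the sample size" and introduces further work, to "perform secondary analyses (described below), which will be published subsequently". That work adjusts the group effect on the de Morton Mobility Index (DEMMI) for each candidate variable and for all together, adds group-by-variable interactions, and fits a logistic regression for compliance. The cognition analyses come after this, with adjustment for a list that includes "depression, health status, nutritional state, self-reported physical activity, pain, medications, length of stay".

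On harms, Data monitoring asks investigators and physiotherapists to report adverse events. Blinding says that information on such events will be given in the manuscript.

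**The concern.** Patients train to contraction failure, with a weight vest at the higher levels (Training intervention, STAND, Heel raise). Pain is therefore an obvious tolerability measure, and it is collected densely. The plan gives it only the role of a nuisance variable.

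This raises two problems. First, a variable that treatment can change is listed for adjustment and interaction in models of the treatment effect, in a form that exists in one arm only. Secondly, the pain data have no stated place in the main paper except through adverse event reports. The trial aims to support implementation in routine care, so readers of a positive result would want to see how well the programme was tolerated.

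**Working it through.** **1. Which pain measure enters the models?** Additional variables describes pain around training. Table 2 describes pain at four visits. The cognition paragraph restricts two covariates, the orientation-memory-concentration test and DEMMI, to their baseline values, but gives pain no time point. The text therefore leaves three candidates: baseline VRS, follow-up VRS and session VRS.

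**2. Each candidate in a model of the group effect.**

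| Measure | Before randomization? | In both arms? | Usable for a between-group effect? |
|---|---|---|---|
| Baseline VRS | yes | yes | yes, as covariate or modifier |
| VRS at discharge, 4 weeks, 6 months | no | yes | no; it may carry part of the effect |
| VRS before and after sessions | no | no | no; it has no value for controls |

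*Follow-up VRS.* In the simplest linear case, let training change pain by *a* and let each unit of pain change DEMMI by *b*. The total effect is the direct effect plus *a × b*. Adjusting for pain removes *a × b*, so the adjusted coefficient no longer estimates the effect of allocation. Common causes of pain and mobility would add further bias. The document gives neither *a* nor *b*, so the size cannot be stated. The plan judges confounding by comparing the unadjusted with the adjusted group effect. With such a covariate, that difference could be mediation misread as confounding.

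*Session VRS.* Controls have no sessions. A complete-case model drops every control, and the group effect is then not estimable. Imputation does not help, because the values do not exist and the control arm holds no data from which to impute them.

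**3. What the main paper is assured of containing.** The analyses assigned to it are the primary mixed model, similar analyses of the secondary outcomes, adjustment for baseline DEMMI, adjustment for length of stay, and the per-protocol analysis. None uses pain, and pain is not one of the six secondary outcomes.

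**4. How much pain data there would be.** Assume 40 trained patients (half of the maximum of 80) and all 12 home sessions: 40 × 12 × 2 = 960 ratings, plus those from hospital sessions. Visits give up to 80 × 4 = 320 ratings. These are counts of data, not of error.

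**5. Precision of a between-arm comparison.** The plan's 27 per arm reproduces. With a difference of 10, SD 12.8, two-sided 5% and 80% power, the normal approximation gives 26. The two-sample *t* test gives 26.71, hence 27, with power 0.804.

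With 27 per arm and the same share *p* with pain in each arm, the 95% CI half-width is 1.96 × √(2p(1−p)/27):

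- p = 0.10: 1.96 × √(0.18/27) = 0.160
- p = 0.30: 1.96 × √(0.42/27) = 0.244
- p = 0.50: 1.96 × √(0.50/27) = 0.267

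The shares are assumptions; the document gives none.

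**The case against.** A reader might infer that the main paper would report no pain harm at all. The document does not support that. Every session is supervised one to one, adverse events are to be reported by staff and described in the manuscript, and reporting is to follow CONSORT with the non-pharmacological extension. The sentence assigning analyses to the main paper also does not exclude others. The article lists no summary of load, exercise level or protein intake either, so its silence on a pain table may be no more than condensation. Descriptive pain summaries may stand in a fuller plan that is not shown.

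A reader might also infer that the plan is set to adjust a harm away. That goes too far as well. The document does not say which pain measurement enters the models, and a suitable one, baseline VRS, is scheduled. The primary analysis is unadjusted, and no analysis listed for the main paper adjusts for pain.

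The compliance regression is a fair use of session pain. Compliance is defined by completed sessions, so that question lies within the trained arm, and a ban on session pain in all later analyses would do damage. Finally, a comparison with an interval of ±16 to ±27 points could neither establish nor exclude a modest excess of pain.

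These points narrow the finding without removing it. A fuller plan with pain tables would not cure the role and definition given here. The one explicit wording of the variable describes a measure that controls cannot have.

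**Conclusion.** The point holds in a limited form. The article gives pain one role, as confounder or modifier, and words it as pain around training. Used that way, the between-group adjustment and interaction models are biased or cannot be estimated. Table 2 and Additional variables describe different measures and must be reconciled.

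The consequence falls on the later, funding-dependent analyses, including cognition if its position in the text is read as placing it there. The primary result does not change. For the main paper, the supportable statement is that training-related pain is assured of appearing only if it was reported as an adverse event; pain below that threshold has no stated place.

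The conclusion about the models rests on the timing of the measurements and on controls having no sessions, not on any assumed figure. The rating counts and interval widths rest on the stated assumptions. The change is worth making because it costs little.

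**What to change.** 1. In Additional variables and Table 2, separate three measures: baseline VRS, VRS at follow-up visits, and VRS before and after sessions (intervention arm only).
2. In the between-group models for DEMMI, the other outcomes and cognition, admit only baseline, pre-randomization VRS as covariate or modifier.
3. Leave session pain available for the compliance regression, fitted within the intervention arm.
4. In the main paper, report VRS at discharge, 4 weeks and 6 months by arm as a descriptive tolerability outcome, with the between-arm difference and 95% CI.
5. Within the intervention arm, summarise the change in pain from before to after sessions.

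The cost is a few wording changes and one extra table with wide intervals. No new visits, staff, patients or measurements are needed, and nothing in the training itself changes.

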### Data collection

The primary investigator and a team of three assistant investigators will perform all baseline and follow-up assessments. All four investigators are trained physiotherapists with 1 to 15 years of experience.

The admission assessments will be performed on the acute medical admissions ward or on an internal medicine ward at Copenhagen University Hospital, Hvidovre, Denmark, within the first 48 h after admission. All follow-up assessments will be performed in the patient’s own home, and the same investigator will assess the same patient at all assessments whenever logistically possible, to promote patient retention.

During each training session the supervising physiotherapist will complete an exercise diary consisting of information about the level of exercise attained according to the progression models, the extra load added (kg), and the number of sets and repetitions performed at each level. Self-reported pain will be registered immediately before and after each training session by the use of the VRS. Moreover, the physiotherapist will register reasons for non-participation as well as the amount of protein consumed after each training session. The patient time line including data collection is presented in Table 3.

**Table 3 Tab3:** Patient timeline

	Study period						
Time point	Admission	Baseline	Hospital intervention	Discharge assessment	Home intervention	4-week assessment	6-month assessment
		≤48 h after admission	Daily during hospitalization	In patient’s home	3 times per week for 4 weeks in patient’s home	In patient’s home	In patient’s home
Enrollment							
Eligibility screen	X						
Informed consent	X						
Study groups							
Strength training		X	X	X	X	X	X
Control		X		X		X	X
Assessments							
Baseline assessment^a^		X					
Primary outcomes		X		X		X	X
Secondary outcomes		X		X		X	X
Descriptive variables and possible confounders and modifiers		X		X		X	X

^a^See Table 2 for a detailed description of assessed variables

### Compliance

High compliance with the intervention is defined as completion of 80 % of all training sessions with a minimum of two sets performed per session.

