### Intervention group

Patients in the intervention group will receive 1:1 supervised progressive strength training daily on weekdays during hospitalization and three times per week for 4 weeks (12 training sessions, 1:1 supervised) after discharge. To account for possible cancellations, i.e. due to illness or other obstacles for training completion, distributing the 12 in-home training sessions over a maximum of 5 weeks will be allowed. The training will take place in the patient’s bedroom during hospitalization and in the patient’s own home after discharge.

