#### Protein supplement

In this study, protein is considered as an integral part of strength training to optimize the anabolic response after training. Therefore, immediately after each training session the patient will be asked to consume an oral protein supplement (Nutridrink Compact Protein from Nutricia A/S) containing 18 g milk-based protein and 300 kcal.

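### One pooled compliance rule selects the per-protocol set, so its discharge contrast rests mainly on attendance after the discharge test, and the supplement does not count

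*Protocol article*

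**What the plan says.** The Compliance section gives a single criterion: "High compliance with the intervention is defined as completion of 80 % of all training sessions", "with a minimum of two sets performed per session". It does not separate hospital from home and has no element for the supplement.

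The Intervention group section sets the sessions that enter the denominator: "1:1 supervised progressive strength training daily on weekdays during hospitalization", and then "three times per week for 4 weeks (12 training sessions, 1:1 supervised) after discharge". The home number is fixed; the hospital number varies with the stay.

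Under Secondary and supplementary analyses, the unadjusted repeated model is run again per protocol, "comparing patients who have fulfilled the compliance criteria with the control group", and this is among the analyses promised for the main paper. The section on the primary analysis shows that this model takes three differences from baseline: discharge, 4 weeks and 6 months. The Blinding section places the discharge test before the first home session.

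On the supplement, the Protein supplement section says that "protein is considered as an integral part of strength training to optimize the anabolic response after training", and the Data collection section has the physiotherapist record "the amount of protein consumed after each training session".

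**The concern.** One flag, built over the whole programme, is applied to a model whose first contrast is measured before most of the programme has taken place. For the discharge contrast, a patient counts as having followed the protocol largely because of what happened afterwards. If patients who are more mobile at discharge also attend more home sessions, membership depends on the outcome being compared, while the control group is taken whole. The per-protocol effect at discharge could then include patients with no hospital training and exclude patients who had all of it.

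There are two lesser mismatches with the stated aim, which is training plus protein begun in hospital and continued at home. Home attendance alone can sometimes satisfy the rule. A patient who never took the supplement can satisfy it at any length of stay.

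At stake is how the per-protocol result in the main paper is read. The planned logistic regression with compliance as its outcome, which is conditional on further funding, would inherit the same definition.

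**Working it through.** The plan gives no figure that depends on this rule. Its one calculated figure, 27 per arm, reproduces (two-sided t test, difference 10, SD 12.8: 26.7, rounded up to 27) and plays no part below.

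**Inputs.** Home sessions: 12 (Intervention group). Threshold: 80 % of all sessions, read as the pooled total because no other denominator is given (Compliance). Scheduled hospital sessions: *h*, one per weekday of stay after randomization. The article gives no length of stay, so *h* is an assumption, shown as a range.

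**Formulas.** Sessions required = 0.80 × (12 + *h*), rounded up. Compliance with every home session and no hospital session = 12/(12 + *h*). The same fraction is the share of the denominator that falls after the discharge test.

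| *h* | Total | Required | 12/(12 + *h*) | Qualifies with no hospital session? |
|---|---|---|---|---|
| 1 | 13 | 11 | 92.3 % | yes |
| 2 | 14 | 12 | 85.7 % | yes |
| 3 | 15 | 12 | 80.0 % | yes |
| 4 | 16 | 13 | 75.0 % | no |
| 5 | 17 | 14 | 70.6 % | no |
| 10 | 22 | 18 | 54.5 % | no |

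**Discharge contrast.** Across this range, between 92.3 % and 54.5 % of the sessions that decide membership come after the discharge outcome is measured. Two patients with *h* = 2 show the effect:

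- 2 of 2 in hospital, 9 of 12 at home: (2 + 9)/14 = 78.6 %, dropped.
- 0 of 2 in hospital, 12 of 12 at home: 12/14 = 85.7 %, kept.

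At the discharge test the first has had all the scheduled training and the second none.

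**No hospital training.** At *h* = 2 or 3 the required number is 12, so a patient with no hospital session must complete all 12 at home. At *h* = 1 the required number is 11, so 11 of 12 is enough (11/13 = 84.6 %). From *h* = 4 at least one hospital session is needed.

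**Supplement.** The rule has no term for it, so zero intake qualifies at every *h*.

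**The case against.** The best defence is that the rule measures training compliance and does so coherently. Table 1 describes the intervention as strength training without naming protein, and the Study design section speaks of a strength training program. For the 4-week end point, a pooled count of sessions is a reasonable measure of dose. That stands, and it is why the pooled rule need not be replaced there. The patient with 9 of 12 home sessions is wrongly excluded only from the discharge contrast.

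It can also be said that the article takes the effect during hospitalization from the primary, intention-to-treat model and does not expressly promise a per-protocol discharge effect. That is fair. But the same repeated model is to be rerun per protocol and reported in the main paper, it produces that contrast, and nothing excludes it.

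A reader might infer that hospital sessions are usually few, so that the per-protocol set would largely consist of home-only patients. The article does not support this. Weekday-only training and a baseline up to 48 h after admission make small *h* plausible, but no length of stay is given, and the plan for replacing activity monitors allows for stays beyond 7 days. The case also needs full or nearly full home attendance.

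A reader might also conclude that 80 % should be required in each phase. That is a debatable trade-off. For *h* of 4 or less, 80 % rounds up to every hospital session, so one missed because of illness would exclude the patient and could favour healthier ones. It also gives no rule when no session was scheduled.

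**Conclusion.** The point holds in a limited form. Its firm part is the discharge contrast: the pooled rule selects patients for that comparison mainly on sessions held after the outcome was measured, for any *h* below 12. This rests only on the order of events and the definition stated in the article.

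That a patient without any hospital session can qualify is true for one to three scheduled sessions, given 12 of 12 at home (11 of 12 when one was scheduled). How many patients this concerns cannot be told from the article. The absence of the supplement from the rule needs no assumption about length of stay, but whether it belongs in a per-protocol definition is partly a matter of choice, so it calls for a sensitivity analysis and not a new main rule.

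The intention-to-treat primary result and the sample size are unaffected. The matter deserves correction because the per-protocol analysis goes into the main paper.

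**What to change.** 1. For the per-protocol discharge contrast, define compliance by in-hospital sessions only, or state that this contrast will not be reported per protocol. If it is kept, say in advance how patients with no scheduled hospital session are handled.
2. Keep the pooled 80 % rule for the 4-week contrast.
3. Add a sensitivity per-protocol set at 4 weeks that also requires in-hospital participation where at least one session was scheduled. Class patients with none scheduled on home sessions alone.
4. Add a second sensitivity set that requires the supplement to have been consumed after 80 % of attended sessions. Because amounts are recorded, state what amount counts as consumed.
5. Report how many per-protocol patients had no in-hospital session.

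The change is to analysis wording only. The Data collection section already has sets, repetitions, reasons for non-participation and protein amounts recorded, and the article reports an earlier change to the analysis plan made while the study was still blinded. The cost is smaller sets with wider intervals, starting from about 27 patients per arm, and possible selection of healthier patients set against an unselected control group. These analyses should therefore stay supplementary.
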